### Bias control

To minimize selection bias, a systematic three-step recruitment procedure (screening, informed consent, and baseline assessment) will be implemented with independent review by a multidisciplinary team. To address follow-up bias, a hybrid surveillance strategy combining telephone interviews and outpatient visits will be employed, with a target follow-up completion rate of ≥ 85% and active tracing of participants lost to follow-up. Confounding bias will be controlled through multivariable regression models incorporating documented potential confounders, with effect modification explored in prespecified subgroup analyses. To mitigate performance and detection bias, outcome assessors will be blinded to baseline results; all primary outcome events will be adjudicated by an independent Endpoint Adjudication Committee in a blinded manner; and all neuroimaging data will be independently reviewed by two radiologists. The study has been prospectively registered on an international clinical trial registry and will be reported in accordance with the STROBE statement.

### Sample size calculation

The sample size was determined based on 5-year consciousness recovery rates reported in the existing literature on prolonged disorders of consciousness. Chen et al. (13) reported a 5-year consciousness recovery rate of 42.3% in a prospective cohort of Chinese patients; a systematic review by Giacino et al. (14) indicated recovery rates of approximately 35–50% among patients with pDoC following TBI; and a recent longitudinal study by Yan et al. (15) reported a 5-year cumulative recovery rate of 48.7%. Given that the present study enrolls a mixed-etiology cohort (traumatic and non-traumatic) and employs a competing-risk analytical framework, a conservative 5-year cumulative incidence rate of 34% (annual event rate: 8%) was adopted as the basis for sample size estimation, ensuring adequate statistical power. Assuming a hazard ratio (HR) of 1.3, two-sided *α* = 0.05, 80% statistical power, and an exposure proportion of 30%, the required number of events was calculated as 544 using the Schoenfeld formula. Adjusting for an anticipated 15% loss to follow-up over the 5-year period, the target sample size was determined to be 1,000 participants. This sample size will ensure adequate statistical power for the primary survival outcome, support detection of secondary outcomes (functional recovery and quality-of-life changes), enable the identification of moderate effect sizes (Cohen’s *d* ≥ 0.5 or OR ≥ 1.5), and accommodate prespecified subgroup analyses. Prespecified subgroup analyses will evaluate the influence of age, sex, and baseline severity; assuming a subgroup prevalence of 30% and an event rate consistent with the overall cohort, ≥ 80% power will be achievable for detecting HR ≥ 1.5 within each subgroup.

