### Study objectives

This study aims to systematically characterize the 5-year natural history of pDoC through a prospective cohort design, thereby bridging the critical evidence gap stemming from the absence of large-scale, long-term follow-up investigations. The specific objectives are as follows:To determine the rates of consciousness recovery, all-cause mortality, and major cardiovascular events over a 5-year follow-up period in patients stratified by initial level of consciousness (VS, MCS−, and MCS+); primary comparisons will be conducted at the VS vs. MCS level, with MCS − vs. MCS + differentiation examined in prespecified subgroup analyses.To identify etiology, injury severity (GCS at admission), time from injury to enrollment, Coma Recovery Scale–Revised (CRS-R) subscale profiles, and neuroimaging indices as independent predictors of consciousness recovery and unfavorable outcomes.To develop and validate a multimodal prognostic prediction model integrating clinical, neuroimaging, and biomarker data.

The primary research question of this study is: among patients with prolonged disorders of consciousness (VS or MCS ≥ 28 days post-acute brain injury), does baseline consciousness level (VS vs. MCS) independently predict 5-year consciousness recovery trajectory, after adjustment for etiology, injury severity, and neuroimaging characteristics?

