## Statistical analysis methods

### General principles and descriptive statistics

All statistical analyses will employ two-sided tests with a significance threshold of α = 0.05, and results will be reported with 95% confidence intervals. Bonferroni correction or false discovery rate (FDR) adjustment will be applied to control Type I error inflation in the context of multiple comparisons. Multivariable regression models will be constructed within the competing-risk framework to identify independent prognostic predictors of consciousness recovery, as detailed in the Primary Analysis subsection below. Separately, a dedicated multimodal prognostic prediction model will be developed and validated using a three-stage hierarchically nested approach incorporating LASSO-based variable selection and bootstrap internal validation (1,000 resampling iterations); the C-index will serve as the primary discrimination metric. The full construction procedure for this prediction model is described in the dedicated subsection below.

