### Primary analysis

For the primary outcome of consciousness recovery, a competing-risk analytical framework will be applied, in which consciousness recovery is designated as the event of interest and all-cause mortality as the competing risk event. Cumulative Incidence Functions (CIFs) will be estimated, and the Fine-Gray subdistribution hazard model will be used to assess the influence of each predictor on the subdistribution hazard of recovery. For the single-endpoint outcome of all-cause mortality, Cox proportional hazards regression will be employed. Covariates will be introduced in a stepwise fashion across five models: Model 1 (unadjusted); Model 2 (adjusted for demographic variables: age and sex); Model 3 (Model 2 plus clinically relevant injury-related variables: etiology [TBI vs. HIE vs. cerebrovascular vs. metabolic/toxic encephalopathy vs. other], GCS at acute admission, and time from injury to enrollment); Model 4 (Model 3 plus baseline CRS-R total score and neuroimaging indices [DTI-FA and fMRI-DMN connectivity]); and Model 5 (fully adjusted model incorporating all prespecified covariates: age, sex, educational level, comorbidities, etiology of brain injury, GCS at acute admission, time from injury to enrollment, baseline CRS-R total score, and neuroimaging indices). Covariate selection will be guided by directed acyclic graph (DAG) construction and prior literature evidence to avoid bias introduced by over-adjustment of mediators and colliders.

The proportional hazards assumption will be tested using Schoenfeld residuals and log–log survival plots; violations will be addressed through stratified Cox models, time-varying covariates, or restricted cubic splines. Results will be expressed as hazard ratios with 95% confidence intervals. Kaplan–Meier curves will be used to visualize survival probabilities across exposure groups, and forest plots will be employed to display effect estimates and their trends across adjusted models.

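### The 544-event target carries 80% power for the unadjusted VS vs MCS comparison only; the primary question is an adjusted one, and its power is lower by an amount the protocol does not state

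*Protocol article*

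**What the plan says.** Under Sample size calculation, the protocol article takes a 5-year recovery incidence of 34% and continues: "Assuming a hazard ratio (HR) of 1.3", with a two-sided 5% level, 80% power and 30% exposed, "the required number of events was calculated as 544 using the Schoenfeld formula". After allowing for "15% loss to follow-up over the 5-year period, the target sample size was determined to be 1,000 participants". The section then says that this size gives adequate power for the primary survival outcome. It mentions no correlation between the exposure and other covariates, and it does not say which exposure the 30% describes or which regression model the calculation serves.

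Under Study objectives, the primary research question is: "does baseline consciousness level (VS vs. MCS) independently predict 5-year consciousness recovery trajectory, after adjustment for etiology, injury severity, and neuroimaging characteristics"? The Exposure variable section names baseline VS or MCS as the primary exposure; it is observed, not assigned.

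Under Primary analysis there are five models. Model 1 is unadjusted. Model 2 adds age and sex. Model 3 adds etiology, acute GCS and time from injury. Model 4 adds baseline CRS-R total score together with DTI and fMRI indices. The last is "Model 5 (fully adjusted model incorporating all prespecified covariates" and keeps all of these. Under Study population, the diagnosis is assessed with the CRS-R.

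**The concern.** The Schoenfeld formula in its plain form gives the events needed to compare two groups when group membership is unrelated to anything else in the model, as after randomisation. Here membership is a clinical state that the plan expects to travel with etiology, injury severity and imaging; that is why it adjusts for them. When the exposure is correlated with the covariates, less independent information about it remains, and the events needed rise by the factor 1/(1 − R²), where R² is the share of variance in the VS/MCS indicator explained by the other covariates.

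The imaging indices named in the primary question enter only in Models 4 and 5, and those models also contain the CRS-R total. Exposure and covariate then come from the same instrument, so R² = 0 cannot be defended for that contrast.

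What is at stake is how a null result is read. If readers believe that the adjusted comparison had 80% power at HR 1.3, a non-significant result may be taken as evidence that consciousness level adds nothing beyond etiology and imaging.

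**Working it through.** **Inputs from the protocol.** HR 1.3; two-sided α = 0.05; power 80%; exposed share p = 0.30, so p(1 − p) = 0.21; 544 events; 5-year incidence 34%; loss 15%; N = 1,000. **Assumed:** R², which the protocol does not give, shown from 0 to 0.4; HR 1.3 read as the adjusted ratio; the 30% read as the VS/MCS split.

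**Step 1: the plan's figure.** Events = (1.960 + 0.842)² / [0.21 × (ln 1.3)²] = 7.849 / (0.21 × 0.06883) = 543. This agrees with 544 to within rounding. A one-sided test would give 428 and an equal split 457, so the plan used the plain two-sided formula at 30% exposed, with no inflation. Power at 544 events is 80.1%.

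**Step 2: the adjusted contrast at 544 events.** Events needed = 543 / (1 − R²). Power = Φ(√[544 × 0.21 × (1 − R²)] × ln 1.3 − 1.96).

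| Assumed R² | Events for 80% power | Power at 544 events, formula | Power, simulation |
|---|---|---|---|
| 0 | 543 | 80.1% | 80.2% |
| 0.1 | 604 | 75.8% | 80.0% |
| 0.2 | 679 | 70.8% | 73.9% |
| 0.3 | 776 | 65.0% | 68.6% |
| 0.4 | 905 | 58.4% | 59.7% |

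The simulation fitted a Cox model with three prognostic covariates and a conditional HR of 1.3 (N = 1,600, about 542 events, 2,000 runs per point, Monte Carlo error about 1 point). A smaller run of 400 per point, with error about 2 points, gave 81.5%, 80%, 75% and 71.5% at R² = 0 to 0.3. Both show a milder loss than the formula: nothing visible at 0.1, then about 6 points at 0.2, 12 at 0.3 and 20 at 0.4 in the larger run.

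**Step 3: the events the study will yield.** On the plan's own rate, 1,000 × 0.34 = 340 events. If the 15% loss removes events in proportion, 340 × 0.85 = 289. The HR detectable with 80% power is exp{2.802 / √[D × 0.21 × (1 − R²)]}, where D is the number of events.

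| Assumed R² | Detectable HR, 340 events | Detectable HR, 289 events | Power at HR 1.3, 340 events | Power at HR 1.3, 289 events |
|---|---|---|---|---|
| 0 | 1.39 | 1.43 | 60.1% | 53.3% |
| 0.1 | 1.42 | 1.46 | 55.7% | 49.2% |
| 0.2 | 1.45 | 1.50 | 50.9% | 44.8% |
| 0.4 | 1.53 | 1.59 | 40.4% | 35.3% |

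**The case against.** Several points can fairly be made for the plan.

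- The figure of 544 is correctly computed. That stands: the fault is the fit of the formula to the question, and this is not an arithmetic error.
- The sample size section never says that its 80% belongs to Model 4 or 5. A reader might infer that the plan explicitly promises 80% power for the adjusted effect; it does not. The link comes from reading the power statement beside the primary research question, and Model 1, which the formula does fit, is also to be reported. But the section offers one power figure for the primary outcome and does not limit it to the unadjusted comparison.
- R² appears nowhere in the protocol. A reader might infer that 544 events must miss 80% by a material margin. The documents do not support that: at R² = 0.1 the simulation shows no visible loss. The simulation also used a Cox model, while the plan uses Fine-Gray for recovery.
- A reader might go further and treat VS/MCS as a cut of the CRS-R total, which under a normal score gives R² near 0.58 and power near 45%. That should not be used. The protocol does not define VS/MCS as a cut of the total, the primary question does not list the CRS-R total among its adjustments, and the plan says covariates will be chosen to avoid over-adjustment. Adjusting an exposure for its own scale is a question of what is being estimated, and more events would not cure it.
- The gap between 544 required events and the 340 expected is the larger defect. It takes power from 80% to 60% with no assumption about R². This stands. Still, enlarging the study to 544 events would leave a target sized for Model 1.

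**Conclusion.** The point holds in limited form. The requirement of 544 events supports 80% power at HR 1.3 for an unadjusted VS vs MCS comparison, or for an exposure uncorrelated with the covariates. It does not carry over to the adjusted contrast in the primary question, because some correlation is built into the models that contain imaging. The loss at 544 events cannot be fixed from the documents. It is negligible to about 4 points at R² = 0.1 (simulation and formula), about 6 to 9 points at 0.2, and about 20 to 22 points at 0.4. These figures rest on the assumed R², on reading the 30% as the VS/MCS split, and on HR 1.3 as the adjusted effect. The adjustment loss adds to the event shortfall and is the smaller of the two over most of this range.

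**What to change.** In the sample size section: (1) label 544 as the requirement for the unadjusted comparison (Model 1); (2) state which exposure the 30% describes; (3) for the adjusted contrast, restate power or detectable HR over a range of R² such as 0.1 to 0.4, at the events that 1,000 participants will yield on the plan's own rate. The second table above gives these: detectable HR about 1.42 to 1.53 with 340 events, or 1.46 to 1.59 with 289. R² can be estimated from the baseline data of early enrollees without looking at outcomes. Make the change together with the correction of the event shortfall, since both alter the same sentence.

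The cost is a few sentences and a less favourable stated power. No extra patients are needed if the claim of 80% power at HR 1.3 is withdrawn for the adjusted contrast. Keeping that claim would need 604 to 905 events for R² of 0.1 to 0.4, which at 34% incidence means about 604 / 0.34 = 1,776 to 905 / 0.34 = 2,662 participants before loss.

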## Methods

### Study design and setting

The Prolonged Disorders of Consciousness Cohort (PDOCC) study is a single-center, prospective cohort study designed to systematically characterize the 5-year natural history and prognostic determinants of VS and MCS. A total of 1,000 eligible participants are planned for enrollment between June 2026 and May 2029, with longitudinal follow-up conducted over 5 years via structured telephone interviews at 3-month intervals. The study will be conducted at the Department of Rehabilitation Medicine, Guangdong Sanjiu Brain Hospital. The enrollment period spans from June 1, 2026 to May 31, 2029 (36 months). The follow-up period is calculated from each participant’s date of enrollment and extends for 60 months, with full cohort follow-up to be completed by May 31, 2034. Data collection encompasses a baseline assessment at enrollment and scheduled follow-up visits at 3, 6, 12, 24, 36, 48, and 60 months. The study protocol has been approved by the Institutional Review Board of Guangdong Sanjiu Brain Hospital (Ethics Approval No. 2026-01-073). Written informed consent will be obtained from all participants or their legally authorized representatives (LARs) prior to enrollment.

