Despite these methodological strengths, several limitations warrant acknowledgment. As a single-center study, this protocol may face limitations in sample representativeness, and caution will be required when generalizing findings to other regions of China. Additionally, extended follow-up duration may increase attrition rates, and certain self-reported variables may be susceptible to recall bias. Detailed contingency measures have been developed to address these risks: an additional 20% recruitment buffer has been incorporated into the sample size calculation to accommodate anticipated dropout; multiple imputation by chained equations will be employed to handle missing data, and robustness will be evaluated using pattern mixture models and tipping point analyses; baseline characteristics will be compared between participants lost to follow-up and completers, with inverse probability weighting applied to correct for potential selection bias; objective medical records will be prioritized over self-reported data wherever feasible; and sensitivity analyses will be performed to validate the reliability of primary conclusions. The limitations of the single-center design will be explicitly acknowledged in the discussion, and future multicenter validation research will be recommended.

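### At the protocol's own 34% recovery incidence, 1,000 patients yield about 289 to 340 recovery events, not the 544 required, so power for HR 1.3 is about 53% to 60% rather than 80%

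*Protocol article*

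**What the plan says.** All the inputs and the result stand in one paragraph, Sample size calculation. It cites five-year or overall recovery rates of 42.3%, about 35–50% (after TBI) and 48.7%, and then settles on a lower planning value: "a conservative 5-year cumulative incidence rate of 34% (annual event rate: 8%) was adopted as the basis for sample size estimation". The test assumptions follow: "Assuming a hazard ratio (HR) of 1.3, two-sided" alpha of 0.05, and "80% statistical power, and an exposure proportion of 30" per cent. From these, "the required number of events was calculated as 544 using the Schoenfeld formula". The last step is: "Adjusting for an anticipated 15% loss to follow-up over the 5-year period, the target sample size was determined to be 1,000 participants". The paragraph concludes that this size gives adequate power for the primary outcome. It adds that a subgroup with 30% prevalence, at the cohort's overall event rate, would have at least 80% power for an HR of 1.5 or more.

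Two other places bear on the point. Study design and setting fixes the follow-up: "The follow-up period is calculated from each participant’s date of enrollment and extends for 60 months". The Discussion, in its limitations paragraph, describes the allowance for dropout differently: "an additional 20% recruitment buffer has been incorporated into the sample size calculation to accommodate anticipated dropout".

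**The concern.** The paragraph gives a number of events needed, a probability that a patient has the event, a loss rate and a number of patients. These four must fit together, and they do not. If 34% of patients recover within five years, 1,000 patients cannot supply 544 recoveries, even with perfect follow-up.

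What is at stake is the stated power for the primary research question in Study objectives: whether baseline VS versus MCS independently predicts recovery. Readers of the eventual paper would take an 80% chance of detecting HR 1.3 as the design property. On the protocol's own inputs, a true HR of 1.3 would be missed in about 40% to 47% of such studies.

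**Working it through.** **Inputs, all from Sample size calculation:** HR 1.3; two-sided alpha 0.05 (z = 1.960); power 80% (z = 0.842); exposed proportion 0.30; five-year cumulative incidence 0.34; loss 15%; N = 1,000. Study design and setting gives every participant 60 months from enrollment, so the five-year incidence applies to the whole cohort.

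**Step 1. Reproduce the required events (Schoenfeld).**

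d = (1.960 + 0.842)² / [0.30 × 0.70 × (ln 1.3)²] = 543

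The stated 544 differs only by rounding; with z-values 1.96 and 0.84 and ln 1.3 taken as 0.262, the formula gives 7.84 / (0.21 × 0.0686) = 543.9. Other settings do not fit: one-sided 428, equal groups 457, 90% power 727. The event requirement is correct.

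**Step 2. Convert events to patients.**

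- Before loss: 544 / 0.34 = 1,600.
- After 15% loss: 1,600 / 0.85 = 1,882.4, so 1,883.

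Neither is 1,000.

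**Step 3. Events that 1,000 patients give.**

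- No loss: 1,000 × 0.34 = 340.
- Loss spread evenly over five years, with constant rates: λ = −ln(0.66)/5 = 0.0831 and δ = −ln(0.85)/5 = 0.0325; events = 1,000 × λ/(λ + δ) × [1 − exp(−5(λ + δ))] = 1,000 × 0.719 × 0.439 ≈ 316.
- Worst case, where those lost contribute no events: 850 × 0.34 = 289.

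**Step 4. Power and detectable HR.** Power = Φ(√(0.21 d) × ln 1.3 − 1.960). HR detectable with 80% power = exp(2.802 / √(0.21 d)).

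| Scenario | Events | Share of 544 | Power for HR 1.3 | HR detectable at 80% power |
|---|---|---|---|---|
| No loss | 340 | 63% | 60% | 1.39 |
| 15% loss, even | 316 | 58% | 57% | 1.41 |
| 15% loss, no events from those lost | 289 | 53% | 53% | 1.43 |

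**Step 5. Does any other reading lead to 1,000?**

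- 544 events need a recovery rate of 544/1,000 = 54.4% with no loss, or 544/850 = 64.0% if those lost contribute none. Both exceed every cited rate.
- At 50%, the top of the cited ranges: 500 events (77% power) with no loss, 425 (70%) at worst.
- Reading 8% a year as 5 × 8% = 40%: 400 events (67%) with no loss, 340 (60%) at worst.
- Ignoring incidence altogether: 544 / 0.85 = 640.

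**Step 6. Subgroup sentence.** A 30% subgroup has 300 patients: 300 × 0.34 = 102 events, or 102 × 0.85 ≈ 87 at worst. The same formulas with HR 1.5 give:

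- 30% exposed: 41% to 47% power; 228 events needed.
- Equal groups: 47% to 53% power; 191 events needed.

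**The case against.** The strongest reply is that the lower figures are too pessimistic. The Loss to follow-up section censors lost participants at their last valid contact, so recoveries before that date count. This stands: 289 events and 53% power are a worst case, and about 316 events and 57% power is the fairer figure if loss accrues evenly. It does not rescue the claim, because even with no loss at all power is 60%.

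A reader might go further and infer that the 34% ignores death, since 8% a year compounded over five years gives 1 − 0.92⁵ = 34.1%, and that the true power is therefore lower still. The document does not support this. It calls the 34% a cumulative incidence and gives the competing-risk framework as one reason for choosing a value below the cited rates. A subdistribution risk of 8% a year compounds in the same way, so the compounding does not show that death was left out. The figures above take the 34% at face value.

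It can also be said that 15% and 20% are different quantities, a loss rate and a recruitment buffer. That is partly fair: 15% loss needs inflation by 1/0.85 = 1.176, or about 18%. The two statements need harmonising, but this is a side issue, and neither allowance turns 544 events into 1,000 patients.

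Finally, the descriptive event rates and the prediction model do not rest on the HR 1.3 power claim, and results will be reported with 95% confidence intervals. That limits the damage to the stated power for the VS versus MCS comparison and the subgroups. Condensation into an article is no explanation, because the inputs and the result are all printed and disagree.

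**Conclusion.** The power statement is wrong as written. The 544 events are correctly derived, but 1,000 patients supply only 53% to 63% of them at the planning incidence. Power for HR 1.3 is about 60% with no loss, 57% with even loss and 53% at worst. The subgroup claim of at least 80% power for HR 1.5 is also unsupported, at 41% to 53% depending on loss and group balance.

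This rests on the protocol's own 34%, 15% and 30% exposed, on Schoenfeld's formula as the protocol uses it, and, for the middle scenario only, on constant recovery and loss rates. The formula is unadjusted. Models 4 and 5 add the baseline CRS-R total, which is likely to correlate with VS versus MCS, so adjusted power would probably be lower; that is not quantified here. The finding does not show that the cohort is too small for its other objectives.

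**What to change.** In Sample size calculation, keep N = 1,000 and replace the claim of 80% power for HR 1.3 with:

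- expected recovery events: 340 with no loss, about 316 with 15% loss spread evenly, 289 at worst;
- power for HR 1.3: 60%, 57% and 53% respectively;
- HR detectable with 80% power: about 1.39, 1.41 and 1.43.

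Correct the subgroup sentence to the power actually available (41% to 47% for HR 1.5 with 30% exposed, 47% to 53% with equal groups), or delete it. State one dropout allowance, in the same terms, in Sample size calculation and in the Discussion.

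The cost is protocol wording and a less favourable power statement; no extra patients or procedures are needed. If the sponsor prefers to keep 80% power for HR 1.3, the stated inputs require 1,883 participants.

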### Subgroup and interaction analyses

Prespecified subgroup analyses will be conducted based on clinical relevance and potential effect modification, including: age (< 50 years vs. ≥ 50 years), sex (male vs. female), injury type (traumatic vs. non-traumatic), and baseline level of consciousness (VS vs. MCS). Interaction terms (product terms between the exposure variable and subgroup variables) will be introduced into multivariable regression models to formally test the statistical significance of interactions, with a significance threshold of *p* < 0.10. Statistically significant interactions will be further examined through stratified subgroup analyses, with results displayed as forest plots showing HRs and 95% CIs for each subgroup. All subgroup analyses will be characterized as exploratory findings to prevent overinterpretation.

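### The stated power of at least 80% for HR 1.5 within each 30% subgroup is wrong; the plan's own inputs give about 41–47%

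*Protocol article*

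**What the plan says.** The protocol article, section "Sample size calculation", closes with a claim about subgroup analyses by age, sex and baseline severity. Its conditions are "assuming a subgroup prevalence of 30% and an event rate consistent with the overall cohort", and its conclusion is that at least 80% "power will be achievable for detecting HR ≥ 1.5 within each subgroup". The same section also says that the sample size accommodates the prespecified subgroup analyses.

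The other inputs stand in the same section:
- Size: "the target sample size was determined to be 1,000 participants".
- Event rate: "a conservative 5-year cumulative incidence rate of 34% (annual event rate: 8%) was adopted as the basis for sample size estimation".
- Method and exposure: "80% statistical power, and an exposure proportion of 30%, the required number of events was calculated as 544 using the Schoenfeld formula", for a hazard ratio of 1.3.
- Attrition: "Adjusting for an anticipated 15% loss to follow-up over the 5-year period".

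The section on general principles sets the test level: "All statistical analyses will employ two-sided tests with a significance threshold of α = 0.05". The section on subgroup and interaction analyses says that interactions between exposure and subgroup factor are tested at p < 0.10, that significant ones are followed by stratified analyses with a hazard ratio for each subgroup, and that "All subgroup analyses will be characterized as exploratory findings to prevent overinterpretation".

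**The concern.** The full cohort is sized for 544 events to detect HR 1.3. A subgroup of 30% has only a fraction of the cohort's events, and the larger target of HR 1.5 does not obviously make up for that. All the inputs needed to test the claim are in the document.

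At stake is how subgroup results are read. A reader told that each subgroup has at least 80% power may take a non-significant result by age, sex or severity as reasonable evidence against an association of that size. If true power is below one half, an association with HR 1.5 would be missed more often than found. The claim also lends the 1,000 participants a justification that they do not have.

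**Working it through.** **Formulas (Schoenfeld, two-sided α = 0.05).** With p the exposed proportion and d the number of events:
- events needed = (1.960 + 0.842)² / [p(1−p) × (ln HR)²] = 7.849 / [p(1−p) × (ln HR)²]
- power = Φ(√(d × p(1−p)) × ln HR − 1.960)

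**1. Reproduce the plan's own figure.** HR 1.3, p = 0.30, so p(1−p) = 0.21: 7.849 / (0.21 × (ln 1.3)²) = 542.97, i.e. 543 events. The plan states 544, so the method and inputs are the plan's.

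**2. Events available in a 30% subgroup.**
- Patients: 1,000 × 0.30 = 300.
- Events at 34%: 300 × 0.34 = 102.
- With 15% loss: 102 × 0.85 = 86.7.

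**3. Events needed for HR 1.5 at 80% power.** 7.849 / (0.21 × (ln 1.5)²) = 227.3, so 228. To reach this among 300 patients, 228 / 300 = 76% would have to recover. The plan assumes 34%, and the highest rate it cites is 50%.

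**4. Power for HR 1.5 (ln 1.5 = 0.4055).**
- 102 events: Φ(√21.42 × 0.4055 − 1.960) = 46.7%.
- 86.7 events: Φ(√18.207 × 0.4055 − 1.960) = 40.9%.

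**5. HR detectable with 80% power.**
- 102 events: exp(2.802 / √21.42) = 1.83.
- 86.7 events: exp(2.802 / √18.207) = 1.93.

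**6. More favourable readings, all two-sided and within a 30% subgroup.**

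| Reading | Events | Power, 30% exposed | Power, 1:1 |
|---|---|---|---|
| 34%, no loss | 102 | 46.7% | 53.5% |
| 34%, 15% loss | 86.7 | 40.9% | 47.1% |
| 42.3% recovery, no loss | 126.9 | 55.3% | 62.7% |
| 48.7% recovery, no loss | 146.1 | 61.3% | 68.8% |
| 50% recovery, no loss | 150 | 62.4% | 70.0% |
| 30% of the 544 required events | 163.2 | 66.0% | 73.6% |

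None reaches 80%. The complementary 70% subgroup (700 × 0.34 = 238 events) has 81.8% at 30% exposed, and 75.3% after loss.

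**7. Cohort that would support the claim.** 228 / 0.34 = 671 subgroup patients before loss and 671 / 0.85 = 789 after it. Dividing by 0.30 gives a cohort of about 2,235 to 2,630.

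**The case against.** **A different contrast.** The strongest reply is that the 30% prevalence was meant as the proportion p in the formula, with the subgroup factor itself compared across the whole cohort. Power for HR 1.5 is then 92.9% with 340 events (1,000 × 0.34) and 88.5% with 289 (340 × 0.85), so at least 80% would hold. This may be where the figure came from. But it measures the power to show that age, sex or severity predicts recovery. The sentence speaks of power inside each subgroup, and the subgroup section describes stratified hazard ratios. On this reading the sentence still has to be rewritten.

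**The assumptions.** The plan gives 30% exposure for the whole cohort only; carrying it into subgroups is an assumption, and the 1:1 column shows that the conclusion does not depend on it. Multiplying events by 0.85 treats lost patients as contributing no events, whereas the plan censors them at last contact, so 41% is a floor. Where baseline consciousness level is the subgroup factor, it is also the exposure, so a VS versus MCS comparison inside that subgroup does not exist.

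**The exploratory label.** It is fair to say that no primary analysis rests on this sentence and that the plan warns against overinterpretation. That limits the consequence. It does not make a numerical power claim correct, and it sits badly beside a claim of adequate power.

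**Interaction tests.** These are not weaker than the within-subgroup tests at the plan's own threshold. For a ratio of hazard ratios of 1.5 between a 30% and a 70% subgroup, power at p < 0.10 is Φ(√(d × 0.21 × 0.21) × 0.4055 − 1.645): 47.0% with 340 events and 42.2% with 289. They are about as underpowered, no more.

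**Conclusion.** The power statement is wrong as written. For HR 1.5 in a 30% subgroup, power is 41% to 47% against the stated 80% or more. The subgroup has 87 to 102 events where 228 are needed, and the HR detectable with 80% power is 1.83 to 1.93. This rests on 1,000 participants, 34% five-year recovery, two-sided α = 0.05 and 30% exposed within the subgroup; the range covers no loss to full loss of 15% of events. The conclusion survives an even exposure split and every recovery rate the plan cites.

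**What to change.** Replace the last sentence of the sample size section along these lines: with 1,000 participants, 34% five-year recovery and 30% exposed, a subgroup of 30% prevalence is expected to yield about 87 to 102 recovery events; this gives 41–47% power for HR 1.5, and 80% power only for HR of about 1.8 to 1.9 or more; subgroup results will be reported as estimates with 95% confidence intervals. Remove the remark that the sample size accommodates the prespecified subgroup analyses, or limit it to exploratory estimation.

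If the authors meant the subgroup factor as a predictor in the whole cohort, they should say so and give that power separately (88–93% for HR 1.5 at 30% prevalence), without describing it as power within subgroups.

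The new figures depend on the main calculation. At 34%, 1,000 participants give 340 events (289 after loss), short of the 544 required, so if the cohort size or event rate is revised, the subgroup figures must be recalculated with it.

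The cost is one or two sentences, with no change to recruitment, data collection or the analyses.
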